### Availability of data and materials

Anonymized data can be shared in academic cooperations. Request for data can be addressed to the principal investigators with an appropriate research question.

## Discussion

The EVA-Tyrol study is a large-scale research and prevention program targeting cardiovascular health-promotion in adolescents. The planed 2000 participants will represent about 5% of the Tyrolean population at that age and will allow in-depth insights into vascular risk profile and vascular health of a representative Middle European population. The health promotion program used in our trial could realistically be continued at low costs outside the academic study setting. Our study explores novel grounds, as, even though numerous health promotion programs are targeted to the youth, few did prove efficacy. The STRIP study conducted in Turku, Finland, was able to increase the number of ideal cardiovascular health metrics by accompanying children with dietary and later smoking prevention counselling continuously between the age of 7 month and 20 years. Also, dietary counseling of pre-pubertal children with elevated LDL Cholesterol and their parents effectively reduced LDL Cholesterol [34]. However, other health promotion programs for adolescents were less successful [32, 35]. A recent meta-analysis of 30 studies aiming at improving physical activity in children and adolescents could demonstrate only a modest effect of various interventions [35]. In contrast to our study all these interventions focused on a single health behavior and did not provide comprehensive health counseling on multiple cardiovascular risk factors and behaviors.

The descriptive analysis of the EVA-Tyrol study will substantially enhance our understanding of the distribution of vascular risk behaviors and risk factors in subjects with varying social backgrounds (school types, apprentices) as well as sex and age groups and will help to better focus future health promotion programs.

Furthermore, the EVA-Tyrol cohort will allow to explore mechanisms of early vascular ageing by using well-defined surrogate parameters for vascular health (IMT and PWV) and analyze their association with cardiovascular risk factors and health behaviors. High-quality information from the “mother-child booklet” will elucidate the impact of early life weight gain on adolescent vascular health.

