**Methods:**

The EVA-Tyrol study is a population-based non-randomized controlled trial that will prospectively enroll 2000 participants from high schools and training companies in North- and East-Tyrol (Austria) and South-Tyrol (Italy). Participants will be assigned to either an intervention (*n* = 1500) or a control (*n* = 500) group. Intervention group participants will be enrolled at the 10th school grade (mean age 15–16 years), undergo two examinations within a two-year interval, with follow-up at the 12th grade (mean ages 17–18 years). Control group participants will be enrolled at the 12th grade (mean age 17–18 years). Medical examination will include anthropometric measurements, comprehensive lifestyle and dietary questionnaires, a fasting blood sample, high-resolution ultrasound of the carotid arteries, and measurement of carotid-femoral pulse wave velocity. Active intervention will consist of (1) enhancing knowledge about CVDs, (2) individual medical counseling based on the results of the baseline examination, (3) an online health promotion tool and (4) involvement of participants in planning and implementation of health promotion projects. Effectiveness of the intervention will be assessed by comparing the proportion subjects with ideal health metrics as defined by the American Heart Association between study groups.

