### Participants

#### Recruitment

The local education authority (Landesschulrat for Tyrol) will brief all Tyrolean high schools about the project. Subsequently, the schools will be able to apply for study-inclusion. In order to ensure a homogenous regional and social distribution, principals of selected schools will be actively encouraged to participate. Schools and training companies will not receive financial compensation for participation. The two study centers will be Innsbruck (Austria) for North and East Tyrol and Bruneck (Italy) for South Tyrol. Moreover, Tyrolean training companies will be invited to participate. For participating schools and companies a project presentation on the background of CVD and concept of CVRF will be offered. Pupils and trainees will be briefed about the study procedure. In addition, a video summarizing study aims and procedures will be shown.

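### The sample is called population-based and representative, but recruitment is by application, encouragement, invitation and consent, so raw prevalences describe the participating schools and training companies

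*Protocol article*

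**What the plan says.** The abstract's Methods paragraph opens with "The EVA-Tyrol study is a population-based non-randomized controlled trial". Trial aim and objectives lists, first among the primary objectives, an assessment of the health of Tyrolean youth. The Discussion puts the 2000 participants at about 5% of Tyroleans of that age and says, in the same sentence, that they "will allow in-depth insights into vascular risk profile and vascular health of a representative Middle European population".

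The Recruitment section describes how the sample comes about:

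- Briefing: "The local education authority (Landesschulrat for Tyrol) will brief all Tyrolean high schools about the project".
- Entry: "Subsequently, the schools will be able to apply for study-inclusion".
- Encouragement: "In order to ensure a homogenous regional and social distribution, principals of selected schools will be actively encouraged to participate".
- Companies: "Moreover, Tyrolean training companies will be invited to participate".

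Inclusion criteria adds individual consent, with a legal representative's consent for those under 18, and leaves the number of schools and companies open. Outcome measures and statistical analysis treats the prevalence work as descriptive and exploratory.

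**The concern.** A survey objective about Tyrolean youth needs either a sample drawn with known probabilities or a claim limited to those who took part. The article makes the population claim but describes neither a sampling frame nor a selection step. Sites enter because they want to, or because someone urged or invited them, and pupils then opt in. Schools and companies receive no payment, and what they join includes a health-promotion programme, so interest in health could plausibly influence who enters. The quantities to be described are health behaviours and risk conditions, which that same interest may affect.

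What is at stake is how the descriptive results will be read. The Discussion expects them to help focus future health promotion. A reader told that the sample is representative would take a prevalence and its interval as the Tyrolean figure, although the interval reflects sampling error only.

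**Working it through.** **Claim against design.** The claim appears in the abstract and the Discussion. Entry has four steps (all high schools briefed, schools apply, chosen principals encouraged, companies invited), followed by pupil consent. Briefing all high schools gives each a chance to apply but attaches no selection probability. Encouragement has a stated balancing aim, but no quotas, strata or population margins are given. Spread over regions and social groups is not the same as matching the population's proportions.

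**The plan's own figure.** The 5% coverage implies 2000 / 0.05 = 40,000 adolescents. The population count is not given, so this can only be back-calculated. About 95% of the age group is therefore unobserved. The power figures for the group comparison play no part in this point.

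**What coverage does to selection error.** With coverage f,

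population prevalence = f × p(participants) + (1 − f) × p(non-participants),

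so the error of a raw prevalence is (1 − f) × d, where d = p(participants) − p(non-participants). With f = 0.05 this is 0.95d. The documents give no value for d. Over an assumed range:

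| Assumed d (points) | Error of raw prevalence (points) |
|---|---|
| 3 | 0.95 × 3 = 2.85 |
| 5 | 0.95 × 5 = 4.75 |
| 10 | 0.95 × 10 = 9.5 |

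Sample size enters only through f, so recruiting more people by the same route leaves the error almost unchanged while f stays small.

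**Comparison with nominal precision.** The 95% half-width under simple random sampling is 1.96 × √(p(1 − p)/n). At p = 50%:

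| Group | n | Half-width (points) | d at which 0.95d equals it |
|---|---|---|---|
| Both grades pooled | 2000 | 2.19 | 2.19 / 0.95 = 2.31 |
| 10th grade (intervention baseline) | 1500 | 2.53 | 2.53 / 0.95 = 2.66 |
| 12th grade (controls) | 500 | 4.38 | 4.38 / 0.95 = 4.61 |

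The grade-specific rows are the relevant ones, because the two groups are enrolled at different ages. An assumed 3-point gap exceeds the nominal half-width for the 10th grade (2.85 against 2.53) but not for the 12th (2.85 against 4.38). A 5-point gap exceeds both (4.75). Coverage by grade is not stated; if the implied 40,000 split evenly (an assumption), the factor would be 1 − 1500/20,000 = 0.925 and 1 − 500/20,000 = 0.975, close to 0.95. Positive correlation within schools and companies would widen all these intervals.

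**The case against.** Several counter-arguments have weight.

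- *The words can be read more loosely.* 'Representative' grammatically qualifies the population, so it may mean that Tyrol typifies Middle Europe; 'population-based' may mean recruited in the community rather than in clinics. That reading fits the briefing of all high schools, the inclusion of companies and the absence of exclusion criteria. It is possible, but neither term is defined, and the sentence that carries the coverage figure invites the stricter reading.
- *Recruitment is not haphazard.* Encouragement aims at regional and social balance, and the Discussion foresees description by school type, apprenticeship, sex and age. Both soften the problem. Neither addresses self-selection on health interest within those groups.
- *A missing weighting plan is not an error.* Correct. Such detail may sit in a document not shown, and the point does not rest on it. It rests on an asserted property that the stated recruitment does not deliver, which no analysis plan could supply.
- *The magnitude is an assumption times 0.95.* Also correct. The table shows how an error would carry through; it is not evidence that one exists.

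A reader might go further and infer that the published prevalences will be wrong by a known amount or in a known direction, or that one pooled raw figure will be presented as the Tyrolean prevalence. The documents give no data on non-participants and announce no such pooled figure. A reader might also infer that the primary comparison is biased by this route. The point does not show that: volunteer entry limits generalisation, and bias between the groups would need a separate argument.

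**Conclusion.** The point stands as a limit on what the descriptive prevalence objective can conclude. The article attributes to the sample a property that its own recruitment does not provide, and 5% coverage does not supply it. The possible error is about 0.95d, with size and direction unknown. It would exceed the nominal half-width at 50% prevalence once d passes about 2.7 points in the 10th grade or 4.6 points among the 12th-grade controls, under simple random sampling. These thresholds rest on the article's 5% figure, on the planned group sizes and on ignoring clustering. The primary outcome, its test and the sample size are not affected.

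**What to change.** 1. In the abstract and the Discussion, replace 'population-based' and 'representative' with a description of a volunteer sample of schools and training companies with purposive regional and social spread.
2. For the health-survey objective, report prevalences separately for 10th and 12th grade, raw and standardised to the Tyrolean margins of school type or apprenticeship, sex and region, with intervals that allow for clustering within schools and companies.
3. Report participation rates for schools, companies and pupils. These are best logged during recruitment, since refusals are hard to reconstruct later.
4. State that standardisation corrects only for the margins used and not for self-selection on health interest within them.

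The cost is a wording change, a participation log and one weighting step, which assumes that enrolment and apprenticeship counts can be obtained from the authorities. If they cannot, the inference should be restricted to participants. Expect somewhat wider intervals and a more modest claim.

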## Data Availability

Request for data shall be addressed to the corresponding authors.

## Abbreviations

AHA: American heart association
COMET: Competence centers for excellent technologies
CRF: Case report form
ctc: Clinical trial center
CVD: Cardiovascular diseases
CVRF: Cardiovascular risk-factors
Dash: Dietary approach to stop hypertension
ECLIA: Electrochemiluminescenceimmunoassay
EVA: Early vascular ageing
FFG: Austrian Research Promotion Agency
HPLC: High pressure liquid chromatography
IHS: International headache society
IMT: Intima-media thickness
MD: Medical doctor
NCD: Non-communicable diseases
PI: Principle investigator
PWV: Pulse wave velocity
TGKK: Tiroler Gebietskrankenkasse = Tyrolean regional medical insurance
VASCage: Research Center of Excellence in vascular ageing - Tyrol
